**Fig. 2 Fig2:**
[figure not shown]
SPIRIT figure for the PROCAP trial. EQ-5DL EuroQol EQ-5D, PROCAP PROCalcitonin-based algorithm for antibiotic use in Acute Pancreatitis, SPIRIT Standard Protocol Items: Recommendations for Interventional Trials

Patients who become symptomatic (at any point) for infection will undergo PCT assay and follow the PCT algorithm. Clinically symptomatic patients with a low PCT will not receive antibiotics. If there is persisting concern of infection in patients with a low PCT, the test will be repeated at 24 h. Symptomatic patients with a raised PCT will receive antibiotics according to Manchester University Foundation Trust antibiotic policy. The PCT algorithm will be used to guide continuance and discontinuation of antibiotics. In asymptomatic or symptomatic patients with positive microbiology results, it is appropriate to treat positive microbiology results with antibiotics. PCT should be measured before commencing antibiotics. PCT measurement should be used to guide cessation of therapy, either after 48 h, 72 h or 96 h as clinically appropriate. To avoid repeated short courses of antibiotics, if antibiotic use is triggered by the algorithm, use will be continued for at least 48 h and then PCT re-assayed. If there is no clinical evidence of infection at this point, with this second PCT measurement below threshold, antibiotic use will be discontinued. If antibiotics have been prescribed outwith the algorithm, then continued use will be discussed with the consultant hepato-pancreato-biliary (HPB) surgeon under whose care the patient is being treated or with the Chief Investigator. After this discussion, antibiotic therapy may be stopped. The clinician over-ride can be used to either start or stop antibiotics in situations of clinical urgency. Then, the clinician must be either a consultant HPB surgeon or a consultant intensive care physician, and the reason for over-ride will be documented. If patients undergo endoscopic, radiological or surgical procedures which would normally be undertaken under the cover of antibiotic prophylaxis, it is appropriate to do this without PCT measurement. If prophylaxis is merged with therapy, then the PCT measurement for discontinuance will be triggered.

### Selection of PCT cut-off threshold

As with other biomarkers of severity, the usefulness of PCT is influenced by its chosen threshold value and the timing and accuracy of the assay. Although no absolute consensus exists regarding the most appropriate cut-off value for identification of sepsis in acute pancreatitis, Mofidi et al. [25] report a meta-analysis of eight studies using PCT cut-off values > 0.5 ng/ml. Taken together with the recommendations of Schuetz et al. [23] for PCT algorithms in critical care settings, the optimum threshold for PCT for this study is 1.0 ng/ml.

### PCT assay

The Elecys® BRAHMS fully automated PCT immunoassay (BRAHMS Assay; Roche Diagnostics Ltd, Rotkreutz, Switzerland) will be used for the quantitative determination of procalcitonin in serum.

### Standards of general care for all patients with acute pancreatitis

Standard care will follow the current International Association of Pancreatology/American Pancreatic Association (IAP/APA) guidelines for the care of patients with acute pancreatitis [11]. All aspects of care, with the sole exception of antibiotic use, will be the same for patients in both arms of the trial. As PCT measurement is currently not used regularly in this or other hospitals in the NHS for patients with acute pancreatitis, the control arm will represent current standard care. There will be no procalcitonin measurement in patients allocated to this arm.

### Outcomes

i)
***Primary outcome measure***

The primary outcome measure will be the binary outcome: whether antibiotic use occurs during the index stay.ii)***Secondary outcome measures***Safety non-inferiority endpoint all-cause mortalityDays of antibiotic use (for antibiotics initiated during the index stay) defined as any day (24-h period) when antibiotics were prescribed on the patient’s drug prescription chart and administeredClinical infections defined according to the Centers for Disease Control [29]New isolates of multiresistant bacteria (*Clostridioides difficile*, vancomycin-resistant enterococcus (VRE), methicillin-resistant *Staphylococcus aureus* (MRSA), carbapenemase-producing enterobacteriaceae (CPE))Incidence of multiresistant organism bacteraemiaInfection of pancreatic necrosis—defined either as a result of fine needle aspiration (FNA), radiological evidence of gas in a peri-pancreatic collection or positive microbiological cultures from surgical or post-mortem specimensUse of radiological, endoscopic or surgical intervention [30]Survival at 90 days; time-to-event (mortality) survival (Kaplan–Maier)Length of inpatient stay (in total and by level of care: critical care levels II/III, ward-based care)Re-admission to hospital within 6 weeks of onset of index episodeEpisode-related mortality and causeQuality of life assessed by the EQ-5D-5L questionnaire, at enrollment, discharge and 90 days [31]Cost analysis (from an NHS perspective, including inpatient resource use)iii)***Measurement of outcomes***

The primary (superiority) outcome measure will be antibiotic use (binary endpoint: yes or no) during the index stay. Antibiotics prescribed before the index admission (from the referring hospital or community) will be recorded at admission but not included in the primary endpoint.

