One method of distinguishing infection from inflammation is measurement of procalcitonin (PCT) [20]. Historically, calcitonin peptides were thought to be responsible for calcium homeostasis but this is now thought to be a relatively minor physiological role, and a more contemporary appraisal is that procalcitonin is a “hormokine”, sharing characteristics of both hormones and cytokines and having roles in maintaining vascular endothelial tone in response to bacterial infection [20]. The procalcitonin level in the bloodstream of healthy individuals is below the limit of detection (10 pg/ml) using clinical assays. Procalcitonin levels rise rapidly in response to a pro-inflammatory stimulus of bacterial origin and normally fall after successful treatment [21]. PCT is more sensitive than clinical assessment and routine laboratory markers of sepsis (such as leukocyte count and C-reactive protein) in detecting pancreatic infection [22]. Algorithms based on measurement of procalcitonin have emerged as a means of differentiating bacterial sepsis from a systemic inflammatory response in a wide range of settings [23].

A recent Health Technology Assessment (HTA) report evaluated procalcitonin testing as a guide to antibiotic therapy and concluded that further studies are needed before widespread adoption [24]. PCT has also been evaluated as a biomarker in SAP, mainly for early prediction of severity and for identification of patients with a high risk of infected pancreatic necrosis [25].

Qu et al. [26] reported the results of the only randomised controlled trial of a procalcitonin algorithm in severe acute pancreatitis: a single-centre study of 71 patients from China. They compared a PCT-based algorithm for guidance of antibiotic use to routine care in patients with acute pancreatitis. The duration of antibiotic treatment in the PCT-guided group was significantly shorter (10.9 ± 2.8 vs 16.1 ± 2.5 days, *p* < 0.001) without any adverse effects on outcome. Duration of intensive care treatment, overall hospital stay and cost of care were significantly reduced in the PCT-guided group. However, all patients in the control arm were given antibiotics for up to 14 days, which does not reflect current international guideline recommendations. Thus, the findings of this study need to be reproduced in a setting where antibiotic use follows contemporary practice before procalcitonin-based algorithms can be recommended to guide antibiotic use in acute pancreatitis.

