### Data collection

Data collection will use a case report form (CRF) and include source-verifiable data from patient records, including procalcitonin test findings and the list of primary and secondary endpoints. CRFs will be anonymised and contain no individual patient-identifiable information. Patient-level data will be stored by screening and trial log numbers. Data will be recorded on the timeline of the episode, including time from onset of symptoms to admission, days in baseline hospital for tertiary transfers and delay from admission to enrolment. Patients who are discharged and re-admitted within 6 weeks will be regarded as a re-admission for the same episode of care and treatment will be summated. Patients who are re-admitted will be in the same arm as their original allocation. Re-admission elsewhere will be a specific question sought at follow-up (typically at 6 weeks and 90 days). Patients discharged but subsequently admitted elsewhere within 6 weeks will have their pharmacy charts reviewed wherever possible and antibiotic use summated. The trial process and data collection are designed to be minimally burdensome to patients. Clinically, the 90-day follow-up period will complete the involvement of the patient in the trial.

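### Days of antibiotic use stop counting at discharge unless the patient is re-admitted, so a course finished at home is truncated at a time set after randomisation

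*Protocol article*

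**What the plan says.** The relevant statements in the protocol article are these.

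- **Outcomes, secondary measures.** For antibiotics begun in the index stay, a day of use is "any day (24-h period) when antibiotics were prescribed on" the patient's drug chart and were given. Both conditions must be met. Antibiotics prescribed before the index admission are recorded but left out of the primary endpoint. Nothing comparable is said about antibiotics supplied for use after discharge.
- **Data collection.** "Patients who are discharged and re-admitted within 6 weeks will be regarded as a re-admission for the same episode of care and treatment will be" added together. Patients admitted to another hospital within 6 weeks "will have their pharmacy charts reviewed wherever possible and antibiotic use summated". The stated follow-up question concerns re-admission: "Re-admission elsewhere will be a specific question sought at follow-up (typically at 6 weeks and 90 days").
- **Outcomes, secondary measures.** Length of inpatient stay is a separate outcome.
- **Intervention arm protocol.** "The PCT algorithm will be used to guide continuance and discontinuation of antibiotics". Ward re-assays at days 4 and 7 apply to patients still in hospital. Under Standards of general care, the control arm has no PCT measurement.
- **Design.** Patients are blind to allocation; clinicians are not.
- **Outcomes, primary measure.** "The primary outcome measure will be the binary outcome: whether antibiotic use occurs during the index stay".

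**The concern.** The hypothesis covers starting, continuing and stopping antibiotics. The primary outcome is any use, yes or no, so it cannot register earlier stopping. Days of use is the only listed outcome that measures continuation and discontinuation directly, so its counting rule matters more than its place in the list suggests.

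The rule closes the count at discharge for anyone who completes a course at home. That closing point is not fixed by design. It occurs after randomisation, is set by unblinded clinicians, and may itself respond to the intervention. The Background reports of the earlier randomised trial that "Duration of intensive care treatment, overall hospital stay and cost of care were significantly reduced in the PCT-guided group".

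Two distortions are possible:

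- If controls more often leave with days still to take, their total is undercounted and a true reduction shrinks.
- If PCT-arm patients leave sooner while still on treatment, their total is undercounted and a reduction appears, or grows, because of the shorter stay.

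The definition also sits awkwardly with itself. Restricting it to courses begun in the index stay suggests that each course is followed to its end, while requiring a charted and administered dose ends the count when the chart closes.

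**Working it through.** **1. Which days are counted**

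| Day of a course begun in the index stay | Counted? | Source |
|---|---|---|
| Charted and given in the index stay | Yes | Outcomes |
| Given on re-admission within 6 weeks | Yes | Data collection |
| Given in another hospital within 6 weeks | Yes, where charts can be reviewed | Data collection |
| Taken at home from a discharge supply | No | Neither section provides for it |

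A patient re-admitted in mid-course has hospital days counted on both sides of the gap and the home days dropped.

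**2. The plan's own figure**

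The plan gives no expected value, variance or effect for antibiotic days. Its only related figure is the sample size for the primary outcome (60% v 40%, two-sided 5%, 80% power):

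n = [1.96 × √(2 × 0.5 × 0.5) + 0.842 × √(0.6 × 0.4 + 0.4 × 0.6)]² / 0.20² = 96.9, so 97 per arm.

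This agrees with the protocol. It does not depend on how days are counted.

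**3. Days lost per randomised patient**

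From the Sample size section: treated proportions 60% (control) and 40% (PCT, after the 20-point reduction). Assumed, because the document gives neither: the share of treated patients who go home on antibiotics, *s*, and the days they are supplied, *d*.

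Days lost = treated proportion × *s* × *d*.

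- Central case, *s* = 25% in controls, half that in the PCT arm, *d* = 5: control 0.60 × 0.25 × 5 = 0.75; PCT 0.40 × 0.125 × 5 = 0.25. True difference lost: 0.50 day.
- With half the share in the PCT arm, the loss is 0.60*sd* − 0.40(*s*/2)*d* = 0.40*sd*. Over *s* = 10% to 40% and *d* = 3 to 7 it runs from 0.40 × 0.10 × 3 = 0.12 to 0.40 × 0.40 × 7 = 1.12 days.
- With equal shares, it is (0.60 − 0.40)*sd* = 0.20*sd*, from 0.06 to 0.56 day.
- The sign reverses when 0.40 × *s* × *d* in the PCT arm exceeds 0.60 × *s* × *d* in controls, that is, when *s* × *d* in the PCT arm is more than 1.5 times that in controls.
- If *s* = 0 in both arms, nothing is lost.

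**4. Can length of stay alone produce a difference?**

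This is a simulation under assumptions, since the document gives no distribution of stay or course length: log-normal stay with log-SD 0.8, antibiotics begun on day 1, the rest of the course taken at home. Counted days = min(course length, days from start to discharge), per treated patient.

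| True course, control v PCT (days) | Median stay, control v PCT (days) | True difference | Counted difference |
|---|---|---|---|
| 5 v 5 | 7 v 5 | 0 | −0.5 |
| 7 v 7 | 7 v 5 | 0 | −0.8 |
| 10 v 10 | 7 v 5 | 0 | −1.3 |
| 5 v 5 | 7 v 6 | 0 | −0.2 |
| 7 v 7 | 7 v 6 | 0 | −0.4 |
| 10 v 10 | 7 v 6 | 0 | −0.6 |
| 7 v 5 | 7 v 7 | −2 | −1.1 |
| 10 v 7 | 7 v 7 | −3 | −1.1 |

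The first six rows show a difference created by stay; the last two show a real one shrunk. Every patient discharged in mid-course is assumed to finish it at home, so these rows show the mechanism and do not forecast its size.

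**The case against.** The strongest reply has four parts.

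- **The harm is not documented.** No section says how many patients go home on antibiotics, for how long, or whether the arms differ. This stands. Neither the size nor the sign can be read from the document. The earlier trial's shorter stay came with shorter antibiotic duration; the Background does not say that its patients went home on treatment.
- **The count is not confined to the index chart.** A reader might infer that only index-stay days count. The document does not support that: re-admissions within 6 weeks are added, including those elsewhere where charts can be reviewed. This stands, but these are still hospital records and do not recover a course finished at home without re-admission.
- **The rule is defensible and the detail may lie elsewhere.** A charted and administered dose is objective and source-verifiable, whereas a discharge supply is prescription without proof of intake. That is a good reason to keep the present count as a component. It does not make it a measure of course duration. Nor is this an omitted detail: the article states the counting rule, and the rule as stated excludes home days.
- **The consequences are limited.** This is one of many secondary outcomes, and length of stay is reported beside it, so a reader could see whether stay differs. That is true, but seeing a difference in stay does not show how many treatment days were cut off.

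**Conclusion.** The point holds for the secondary outcome of antibiotic days. As defined, that outcome measures days in hospital on antibiotics, and its closing point can differ between arms for reasons other than when treatment stopped. It can shrink a true difference or create one.

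If the PCT arm has half the control arm's share going home on treatment, the loss is about 0.1 to 1.1 days of true difference per randomised patient (0.5 in the central case). With equal shares it is about 0.06 to 0.56. It is nil if no one is discharged on antibiotics, and the sign turns if the PCT arm loses more days than the control arm. The shares and days supplied are assumptions; only the 60% and 40% come from the protocol.

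Two stronger readings are tempting and not supported:

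- **That the bias is known to favour one arm.** The document does not give the figures needed to say so.
- **That the error spreads further.** The primary outcome is any use during the index stay and, like its sample size, does not involve a day count. The economic analysis is deliberately limited to hospital activity, and nothing in that section makes it depend on this count.

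This is a change that should be made because it is cheap and protects the one direct measure of stopping. It does not threaten the trial's main conclusion.

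**What to change.** - Keep the charted-and-administered count, and name it in-hospital antibiotic days.
- Record, for each course begun in the index stay, the number of days supplied on the discharge prescription.
- Report in-hospital days, supplied days and their total separately by arm.

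The cost is one case report form field taken from the discharge prescription and one sentence in the outcome definition. No treatment rule changes. The downside is that supplied days show what was prescribed, not what was taken, which is why the components should be shown as well as the total.

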### Sample size

Based on current audit data, 60% of patients admitted with acute pancreatitis receive antibiotics [13]. A 20% absolute change in antibiotic use would be a clinically important difference. This effect of intervention has been observed in other studies evaluating a procalcitonin algorithm to guide antibiotic use [23, 28]. A study with 80% power and 5% significance (two-sided) would require 97 patients in each arm (194 patients in total). The study will aim to recruit 200 patients. Assuming a 3.6% mortality rate based on unit audit data [13], the sample size provides a 6.6% non-inferiority margin for the safety measure of overall mortality, assuming no change in mortality, 80% power and 95% CI (one-sided). Previous randomised trials of the use of a procalcitonin measurement algorithm to guide antibiotic use in a range of clinical settings as well as a Health Technology Assessment have shown no evidence of harm from this intervention [23, 24]. However, as there has been no previous evaluation of procalcitonin in an all-comers population of patients with acute pancreatitis, it is useful to include a secondary safety outcome with mortality being the most important factor. The choice of a 6.6% non-inferiority margin is a pragmatic choice based on the projected sample size and the estimated population mortality rate of 3.6%.

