### Randomisation

Web-based randomisation will be provided by the Clinical Trials Unit of the University of Edinburgh (https://www.ed.ac.uk/usher/edinburgh-clinical-trials). Allocation will be in a ratio of 1:1 to routine or algorithm-guided care. Randomisation will be stratified by disease severity (mild or moderately severe/severe) and admission pathway (whether or not the patient has their index (first) admission with acute pancreatitis to the Manchester Royal Infirmary (direct) or is transferred from another hospital (tertiary transfer)). A random block size of 4, 6 or 8 will be applied to each stratum. Patients allocated to either arm will be identified by a label placed inside and on the front of the case notes with copy labels used for ward folders.

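### The infected-necrosis definition omits cultures from endoscopic and radiological drainage, so as written it undercounts a secondary outcome

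*Protocol article*

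**What the plan says.** Among the secondary outcomes, infection of pancreatic necrosis is "defined either as a result of fine needle aspiration (FNA), radiological evidence of gas in a peri-pancreatic collection", or positive cultures from two kinds of specimen. After needle aspiration, the rest of the list reads "radiological evidence of gas in a peri-pancreatic collection or positive microbiological cultures from surgical or post-mortem" specimens. The list is an either/or list with no wording such as *for example* or *including*, so it reads as closed.

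The next outcome in the same list is use "of radiological, endoscopic or surgical intervention". The Intervention arm protocol section makes the same three-way distinction when it deals with prophylaxis: "If patients undergo endoscopic, radiological or surgical procedures which would normally be undertaken under the cover of antibiotic prophylaxis". No other section of the article widens the definition of infected necrosis.

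**The concern.** The protocol foresees three routes into a collection and records all three as interventions, but it accepts a culture as proof of infection from only one of them, plus post-mortem. A collection drained endoscopically or under radiological guidance may grow bacteria with no gas on imaging and no needle aspiration. On the wording given, that patient is scored as not having infected necrosis. Yet the Intervention arm protocol section treats positive microbiology as a reason for antibiotics, so the same patient could be treated on that culture and still be absent from the outcome.

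The trial's hypothesis is that antibiotic use falls with no harm to patients. An undercount of a pancreatic infection outcome makes any real excess in the algorithm arm look smaller in absolute terms, and this favours the hoped-for reading.

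**Working it through.** **1. Is the specimen type covered by another word in the definition?**

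| Proof of infection | Counted as written? |
|---|---|
| Fine needle aspiration result | Yes |
| Gas in a peri-pancreatic collection on imaging | Yes |
| Culture, surgical specimen | Yes |
| Culture, post-mortem specimen | Yes |
| Culture, endoscopic drainage or debridement specimen only | Not listed |
| Culture, radiological drainage specimen only | Not listed |

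A broad reading of *surgical* would cover the last two rows. The protocol's own usage is against it: in two places radiological, endoscopic and surgical are named side by side as different things. The gap is limited to patients whose sole proof falls in the last two rows. A drained patient with gas or a positive needle aspirate still counts.

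**2. What does the gap do to the comparison?**

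Let p1 and p0 be the true rates in the two arms, and let s be the share of true cases that meet the written definition. Assume that s is the same in both arms and that there are no false positives.

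- Recorded rate = s × p, which is below p whenever s < 1.
- Recorded risk difference = s × (p1 − p0), which is shrunk by the factor s.
- Recorded risk ratio = (s × p1)/(s × p0) = p1/p0, which is unchanged.

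**3. Can s, p1 or p0 be taken from the documents?**

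No. The article gives no rate of infected necrosis and no split by route of drainage. The rates and missed shares below are assumptions, chosen only to show how the mechanism behaves. They are not estimates for this trial. True rates are set at 16% v 10%. There are 100 patients per arm, from the target of 200 and the statement "Allocation will be in a ratio of 1:1 to routine or algorithm-guided care".

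Half-width = 1.96 × √[r1(1 − r1)/100 + r0(1 − r0)/100], where r1 and r0 are the recorded rates. Odds ratio = [r1/(1 − r1)]/[r0/(1 − r0)].

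| Assumed share missed | Recorded rates | Difference (points) | 95% half-width (points) | Risk ratio | Odds ratio |
|---|---|---|---|---|---|
| 0% | 16.0% v 10.0% | 6.0 | 9.3 | 1.6 | 1.71 |
| 30% | 11.2% v 7.0% | 0.7 × 6 = 4.2 | 8.0 | 1.6 | 1.68 |
| 50% | 8.0% v 5.0% | 0.5 × 6 = 3.0 | 6.8 | 1.6 | 1.65 |

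Every interval includes zero, so under these assumptions the undercount does not turn a clear result into an unclear one. It lowers the estimated excess and also its upper limit: 6.0 + 9.3 = 15.3 points, against 4.2 + 8.0 = 12.2 and 3.0 + 6.8 = 9.8. The trial would appear to rule out more harm than it has.

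**4. Is the design calculation touched?**

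No. It rests on antibiotic use: "60% of patients admitted with acute pancreatitis receive antibiotics", with a 20-point change. For 60% v 40%, 80% power and 5% two-sided, with pooled variance under the null:

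n = [1.96 × √(2 × 0.5 × 0.5) + 0.8416 × √(0.24 + 0.24)]² / 0.20² = (1.386 + 0.583)² / 0.04 = 96.9, so 97 per arm.

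This agrees with the Sample size section and does not involve infected necrosis.

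**The case against.** The strongest reply is that little rests on this outcome. The Outcomes section makes all-cause mortality the safety endpoint. Infected necrosis is one of a long list of secondary outcomes, has no margin, and falls under those that the Analysis plan says will be given summary statistics. That is correct, and it limits the importance of the point.

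Secondly, the missed patient leaves other traces. The drainage is recorded as an intervention, and clinical infections are recorded under Centers for Disease Control definitions. Those definitions are not reproduced, so it cannot be settled whether they catch these cases. Even if they do, the named outcome stays incomplete.

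Thirdly, the reference to a fine needle aspiration result is loosely worded, and an assessor might classify an aspirate taken at drainage under it. The article does not say so. If this was intended, it needs to be written down, or like cases may be scored differently.

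A reader might also infer more than the documents support:

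- *That infected necrosis is the outcome most directly tied to withholding antibiotics.* The Background reports an overall lack of benefit from antimicrobial therapy given to prevent infection of necrosis, so the article does not support that link.
- *That the undercount differs by arm.* Clinicians are not blind, so the route of drainage or the sampling could differ. But the standards of care section says that everything except antibiotic use will be the same in both arms, and nothing in the article suggests a difference.
- *That the treatment effect is weakened on every scale.* With an equal undercount the risk ratio does not move, and in the illustration the odds ratio barely does. The article names a logit link only for the primary endpoint, so the scale for this outcome is open.

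**Conclusion.** The definition is too narrow as written and should be corrected. This is a stated rule that misclassifies some patients, not a detail left to the analysis plan. Patients whose only proof of infection is a culture from an endoscopic or radiological drainage or debridement specimen are not counted, so the outcome rate is understated. The absolute difference between arms is understated too, provided that the missed share is similar in the two arms.

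The conclusion rests on reading the list as closed and *surgical* in the sense that the protocol uses elsewhere. Its size cannot be estimated from the documents. It concerns one secondary outcome and leaves the primary outcome, the sample size and the mortality non-inferiority endpoint untouched.

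**What to change.** Extend the definition so that infection of pancreatic necrosis is recorded when any of these is present:

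- a positive culture from fine needle aspiration;
- a positive culture from the specimen taken at the first radiological or endoscopic drainage or debridement;
- a positive culture from a surgical or post-mortem specimen;
- gas in a peri-pancreatic collection on imaging.

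Apply it identically in both arms and to patients already recruited, working from source records, and complete the re-scoring before any comparative analysis. Also reporting the count under the published wording would keep the change visible.

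The cost is a short change to the outcome definition and the case report form, plus some re-scoring. The Data collection section already relies on source-verifiable patient records. It is assumed here that drainage cultures can be found in them. There is a small risk of counting colonisation as infection, since a culture from a long-standing drain may not reflect infected necrosis. Restricting the rule to the first-drainage specimen limits that risk, so the restriction must stand in the definition itself.
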